## Abstract

**Background:**

Many Polio survivors have reduced mobility, pain and fatigue, which make access to conventional forms of aerobic exercise difficult. Inactivity leads to increased risk of health problems, many of which are prevalent among Polio survivors. Aerobic exercise programmes in Polio survivors should utilise stable muscle groups and should be designed to minimise exacerbation of pain and fatigue. A home-based arm ergometry aerobic exercise programme may represent an affordable and accessible exercise modality, incorporating exercise prescription principles in this group.

**Methods/design:**

This is a prospective, single blinded, randomised controlled trial. There are two arms; exercise intervention using arm ergometers and control. Polio survivors meeting eligibility criteria will be recruited and randomly allocated to intervention or control groups. Participants allocated to the intervention group will receive a small arm ergometer and a polar heart rate monitor. They will carry out a home-based moderate intensity (50-70% HRMax) aerobic exercise programme for eight weeks, following instruction by the treating physiotherapist. Assessments will occur at baseline and after eight weeks and will include tests of physical fitness, activity, energy cost of walking, fatigue and quality of life. Clinically feasible assessment tools including the Six Minute Arm Test, the Physical Activity Scale for People with Physical Disabilities questionnaire, the Physiological Cost Index, Fatigue Severity Scale and the SF-36v2 will be utilised.

**Discussion:**

The efficacy of a home-based arm ergometry programme in Polio survivors will be examined. No previous trial has examined such a programme using a wide range of outcome measures pertinent to Polio survivors. This study will provide new information on the impact of arm ergometry on physical fitness, activity, body composition, fatigue, pain, muscle strength, and health related quality of life. Also, the study will provide information, which at present is lacking, on safety of aerobic exercise in Polio, as potential negative outcomes of activity including loss of muscle strength, increased pain and fatigue will be closely monitored.

**Trial registration:**

Clinicaltrials.gov identifier: NCT01271530

## Background

Epidemics of Poliomyelitis in Ireland in the 1940s and 1950s produced an estimated 7,500 Polio survivors, who have since lived with the residual physical deficits associated with their condition
[1]. Approximately 50 percent of Polio survivors develop a range of specific symptoms, including new muscle weakness, diagnosed as Postpolio Syndrome
[2]. However many more present with reduced mobility, pain and deconditioning, described in the broadest sense as the late effects of Polio. The majority of Polio survivors have some limitation in mobility, which affects their ability to engage in common forms of aerobic exercise, such as walking or cycling. Polio survivors have poor levels of fitness
[3], report low activity levels at leisure
[4] and have low subjective perception of health
[5]. Furthermore, Polio survivors have increased cardiac risk factors such as dislipidemia and increased blood pressure
[6].

Recommendations regarding physical activity in older adults issued by the American College of Sports Medicine (ACSM) and the American Heart Association apply to the majority of Polio survivors, as adults over 50 with a clinically significant chronic condition
[7]. These recommendations state that older adults should engage in 30 minutes of moderate activity five days per week and emphasise the requirement for an activity plan. A recent survey of 47 Irish Polio survivors found that only 34 percent reported exercising at least three times per week
[8]. Fatigue, mobility and pain were the most common reasons for not partaking in regular exercise. In comparison 64% of Irish adults over 45 report moderate to high activity levels, with time identified as the most common barrier
[9].

Inactivity leads to an increased risk of health problems including obesity, type 2 diabetes, hypertension, coronary artery disease, respiratory dysfunction and osteoarthritis
[10]. Many Irish Polio survivors are overweight
[11]. Farbu
[12], found that in a cohort of 85 Polio survivors, 32% had a history of cardiovascular disease and 11% pulmonary disease – diseases, which exercise intervention can ameliorate.

Exercise prescription is complicated in Polio survivors, due to concerns that muscle overuse and intensive training could perpetuate further weakness in weak and overused muscles
[13]. To date, a small number of trials have found that Polio survivors have the potential to increase their aerobic capacity
[14-17]. Treadmill exercise has resulted in an improvement in cardiorespiratory conditioning, with improvements in fatigue and quality of life also reported
[16]. A six-month weekly physiotherapy led class, which included five minutes of cardiovascular exercise on cycle ergometers, also resulted in improvements in cardiorespiratory fitness, without ill effect in most participants
[17]. However these trials used a range of modes of exercise testing and training, which did not adhere to guidelines for exercise testing and prescription in Polio survivors
[14]. A systematic review of exercise in Neuromuscular disease, which included Postpolio syndrome found that the studies examined had insufficient methodological quality
[18].

The ACSM
[19] recommend that stable muscle groups should be utilised for exercise and that with severe or recent onset weakness should not exercise, while the March of Dimes best practice guidelines
[13] recommend not exercising muscle groups where new weakness is being experienced. While well tolerated by some, lower limbs weakness, pain and reduced mobility will commonly limit the ability to exercise comfortably and safely using treadmills or stationary bicycles. Floor or treadmill walking or lower limb cycling may indeed aggravate pain in those with lower limb weakness and altered biomechanics
[20]. Training with an ergometer is likely to be an appropriate form of exercise in patients with good, stable upper limb strength. One small trial of ergometry over 16 weeks resulted in a 19% increase in VO2 max in ten Postpolio patients exercising three times per week
[15], however the impact on other aspects of health was not examined. In addition arm ergometry has been examined as an appropriate mode of exercise in Polio survivors with subjective rate of perceived exertion significantly related to physiologic markers of exercise intensity
[21].

Investigation of responses to aerobic training in patients with neuromuscular disease has been recommended
[22]. There is a requirement for well-controlled, prospective trials of aerobic exercise training in Polio survivors, utilising methods of testing and training appropriate to these patients. Ideally those with chronic conditions should be facilitated by health professionals to become as independent as possible in maintaining and improving their physical condition
[23]. An appropriate aerobic exercise programme may enable Polio survivors to improve physical fitness, enjoy the health benefits associated with exercise
[7] and perhaps reduce fatigue. A convenient and accessible form of exercise is likely to maximise compliance as Polio survivors are advised to exercise when subjective energy levels are good, to avoid exacerbating fatigue
[13,14]. A small ergometer, provided for use at home may be an affordable option meeting these requirements.

The aim of this randomised controlled trial is to investigate the effect of an aerobic exercise programme, carried out in the home environment, using arm ergometers, on Polio survivors. We hypothesise that upper limb aerobic training will result in a significant increase in fitness in exercising Polio survivors compared with Polio survivors allocated to a control group. Completing the exercise programme is also predicted to improve activity, energy cost of walking and health related quality of life without increases in pain and fatigue.

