### Sample size

The sample size for the study was determined based on a hypothesised change in heart rate of eight beats per minute, during the six minute arm test. Change in fatigue was also examined. The change in heart rate was based on reported changes in previous exercise interventions and considered clinically significant
[17,25]. For each calculation power was set at 80%, alpha at 5% and drop-out rate at 15%. The formula N= 2 [(standard deviation)^2^/(difference)^2^ x 7.9 was used. We aim to recruit 120 participants (60 per group). Table 
2 outlines the number of participants required based on the six minute arm test and the fatigue severity scale.

**Table 2 T2:** Sample size calculation

**Outcome measure**	**Clinically significant difference**	**Standard deviation**	**Number of participants required per group**
6MAT (Heart Rate)	8 b/m	14.5	60
FSS	1 point	1.1	48

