Participants will monitor fatigue and pain on 0–10 Visual Analogue Scales. If there is an increase of more than 2 points in upper limb, neck or back pain, or subjective fatigue, the participant will be advised to reduce exercise duration and/or intensity. If this does not result in an improvement, the participant will be advised to contact the treating physiotherapist by phone. This physiotherapist will then make a decision on how to proceed and the participant will be managed appropriately and withdrawn from the study if necessary. All adverse events will be recorded and managed according to a detailed policy. Participants randomised to the control group will be advised to continue with normal activities and will receive physiotherapy care as appropriate.

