### Statistical analysis

Data will be coded and collated in a Microsoft Excel® spreadsheet and Stata 12 will be used for statistical analysis. All analyses will be conducted on an intention-to-treat principle
[49]. Missing data will be managed using the last observation carried forward method. Per-protocol analyses will be performed excluding participants with major deviations from the treatment protocol (defined as less than 50% compliance with treatment). Demographic characteristics and baseline data will be summarised using descriptive statistics and baseline comparability of the groups will be examined. The distribution of the data will be assessed and if appropriate, parametric methods will be used in analysis. Two sample t-tests will be used to compare groups and paired t-tests will be used for within group comparisons. The non-parametric equivalent will be used where data are not normally distributed. A significance level of p<0.05 will be set. The primary analysis will examine the difference between intervention and control groups. A secondary analysis will compare pre and post intervention scores and will include control participants who crossed over to the intervention group.

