## Discussion

This protocol has detailed the process by which the efficacy of a home-based arm ergometry programme in Polio survivors will be examined. No previous trial has examined such a programme using a wide range of outcome measures pertinent to Polio survivors. This study will provide new information on the potential for arm ergometry to form part of a treatment regimen for Polio survivors and will examine the impact on physical fitness, activity, body composition, fatigue, pain, muscle strength, and health related quality of life. Also, the study will provide information, which at present is lacking, on safety of aerobic exercise in Polio survivors, as potential negative outcomes of activity including loss of muscle strength, increased pain and fatigue will be closely monitored. The use of outcome measures that are clinically accessible will add internal validity to the study. The home-based exercise programme, utilising affordable items of equipment, has the potential to facilitate aerobic exercise in Polio survivors, allowing this patient group to take advantage of the benefits of exercise.

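### The prediction of no increase in pain and fatigue has no margin or confidence-interval criterion, so a non-significant difference test cannot by itself support it; the gap is widest for pain

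*Protocol article*

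**What the plan says.** The closing paragraph of the Background puts the main hypothesis on fitness and adds a secondary prediction: activity, energy cost of walking and "health related quality of life without increases in pain and fatigue". The Abstract and the Discussion both present the trial as a source of safety information that is currently lacking. The Discussion adds that "potential negative outcomes of activity including loss of muscle strength, increased pain and fatigue will be closely monitored".

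The Statistical analysis section gives one inferential approach for all outcomes: "Two sample t-tests will be used to compare groups and paired t-tests will be used for within group comparisons". The fallback is of the same kind: "The non-parametric equivalent will be used where data are not normally distributed". The threshold is also common to all: "A significance level of p<0.05 will be set".

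Table 2 gives a clinically significant FSS difference of 1 point with SD 1.1, used only to size a test of difference. Pain has no entry there. The only numerical threshold for pain during the study is in the Intervention section, "If there is an increase of more than 2 points in upper limb, neck or back pain, or subjective fatigue", where it prompts an adjustment of the individual's exercise.

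**The concern.** Saying that exercise does not increase pain or fatigue is a claim about how large a harm has been ruled out. The stated tests ask whether a difference has been shown to exist. When such a test is non-significant, the data may exclude any worsening that matters, or they may be too imprecise to tell. Few evaluable participants and noisy scores both make the second case more likely, and nothing in the stated analysis separates the two.

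Missing data push the same way. Assessments take place only at baseline and eight weeks, and missing values are filled by last observation carried forward. A participant who leaves because of symptoms and has no eight-week assessment therefore enters with zero change. A margin would not cure that, but it is a further reason not to take reassurance from p>0.05.

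At stake is what the trial may say about safety, which the article names as one of its contributions.

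**Working it through.** **Inputs.** From Sample size and Table 2: 60 per group, 15% dropout, 80% power, 5% alpha; 6-MAT heart rate difference 8 b/m, SD 14.5; FSS difference 1 point, SD 1.1. Evaluable per arm: 60 × 0.85 = 51. Assumptions: the alpha is two-sided (the constant 7.9 is close to (1.96 + 0.84)²); SD 1.1 applies to the FSS measure compared (the article does not say whether it refers to scores or changes); those without an eight-week value add no information.

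**The plan's own figure.** The section states "The formula N= 2 [(standard deviation)^2^/(difference)^2^ x 7.9 was used". For the 6-MAT: 2 × 14.5²/8² × 7.9 = 51.9, and 51.9 × 1.15 = 59.7, so 60 per group is reproduced. For the FSS: 2 × 1.1²/1² × 7.9 = 19.1, or 22 to 24 with dropout, depending on rounding. Table 2's 48 matches only as a total for both groups (2 × 24). That is a separate matter and leaves the planned 120 unaffected.

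**Precision for fatigue.** SE = 1.1 × √(2/51) = 0.218. With t = 1.984 on 100 degrees of freedom, the half-width is 1.984 × 0.218 = 0.43 points.

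**Chance that a true FSS worsening is non-significant** (noncentral t, 51 per arm, SD 1.1):

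| True worsening (points) | Missed |
|---|---|
| 0.3 | 72% |
| 0.4 | 56% |
| 0.5 | 38% |
| 0.6 | 22% |
| 1.0 | 0.5% |

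The 0.3 to 0.6 values are illustrations; only the 1 point is in the documents.

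**What a non-significant FSS result can hide.** If p>0.05, the estimate is below 0.43, so the upper limit is below 2 × 0.432 = 0.86, which is under 1 point. This protection depends on precision:
- At 51 per arm it lasts while 2 × 1.984 × SD × √(2/51) < 1, that is, up to an SD of about 1.27.
- At SD 1.1 it lasts down to 39 per arm (limit 0.99) and fails at 38 (limit 1.01).

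**What a margin alone would do.** A 1-point FSS margin requires the estimate to lie below 1 − 0.43 = 0.57.
- With no true effect, this is met 99.5% of the time.
- With a true worsening of 0.4 points it is still met in 78% of trials, which is more often than the test is non-significant (56%).
- Estimates between 0.43 and 0.57 would meet the margin while being statistically significant worsenings.

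A margin therefore needs a companion rule for significant worsening.

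**Pain.** The article gives no SD, so the calculation is in SD units. With SE = √(2/51) = 0.198 SD, a true worsening of 0.5 SD is non-significant about 29% of the time and one of 0.3 SD about 68%. By normal approximation, with no true effect, the power to exclude a margin of 0.5 SD is 71%, and a margin of 0.3 SD, 33%.

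**The case against.** The strongest reply has four parts.

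**No decision rule is stated.** A reader might infer that the investigators will treat p>0.05 as proof of no harm. The documents do not support that. The Statistical analysis section does not say how a non-significant result will be interpreted, and the pain and fatigue statement is a secondary prediction, with the formal hypothesis resting on fitness. This part stands. The defect is that the stated analysis cannot support the prediction; a wrong conclusion has not been announced.

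**Fatigue is well covered.** A reader might also infer that a clinically significant worsening of fatigue could sit unnoticed inside the interval. On Table 2's figures it could not, since a non-significant result has an upper limit of at most 0.86 points against a 1-point difference. This stands too, as long as the SD and the number evaluable hold.

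**Safety does not rest on p-values alone.** Adverse events are recorded under a policy, and participants monitor pain and fatigue on visual analogue scales. That is true and valuable, but it gives no criterion for a comparison of groups. Nor can the individual trigger serve as one: a change of more than 2 points in one person says nothing about what difference in means is acceptable.

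**This is a condensed article.** A fuller analysis plan could contain margins, and their absence here would not by itself be a finding. What remains is that the article states both the prediction and the tests, and the two do not match.

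**Conclusion.** The point holds in a limited form. The prediction of no increase in pain and fatigue is paired only with tests of difference, so non-significance would not by itself support it.

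For fatigue the consequence is small at 51 evaluable per arm and SD 1.1: half-width 0.43 points, and about a 0.5% chance of missing a true 1-point worsening. It grows if the SD exceeds about 1.27 or if fewer participants are evaluable. Smaller worsenings are often missed, but nothing in the documents says that these matter.

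For pain the gap is real and its size in scale units is unknown, because no SD, effect size or margin is given. In SD units, misses of about 29% (at 0.5 SD) and 68% (at 0.3 SD) show that a non-significant pain result would be weak reassurance.

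These figures assume approximate normality, equal variances and 15% dropout. Change is advisable and cheap; the primary analysis and the planned 120 are unaffected.

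**What to change.** In the Statistical analysis section:

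1. State that p>0.05 will not be taken as evidence of no increase.
2. Report the two-sided 95% CI for the exercise-minus-control difference at eight weeks for fatigue and for pain.
3. Claim no clinically significant increase only if the upper limit lies below a prespecified margin.
4. Report any statistically significant worsening as an increase, even when it falls below the margin.
5. For the FSS, use the 1 point already in Table 2.
6. For pain, the sponsor sets and justifies a group-level margin before unblinding, not borrowed from the individual trigger in the Intervention section. If none can be justified, report the pain interval as descriptive only.

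The cost is wording: no added visit, measure or participant. With 51 per arm and SD 1.1, the 1-point FSS margin is excluded 99.5% of the time if exercise has no true effect. For pain, the present sample may be too small for a tight margin. The downside is that some results that would have been described as no increase become inconclusive, chiefly for pain, or for fatigue if its SD proves larger than planned.

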## Methods

### Study design

This is a prospective, single blinded, randomised controlled trial. There are two arms (i) exercise intervention using arm ergometers and (ii) control. It will not be possible to blind the treating physiotherapist or the patient to the exercise intervention; hence the single (assessor) blinded design. The protocol was approved by the Beaumont Hospital Medical Research ethics committee in November 2009. The trial was designed incorporating recommendations of the CONSORT statement
[24]. The flow of participants through the study is represented in Figure 
1. All participants will receive usual Physiotherapy care, which does not routinely include arm ergometry. Participants in the control group can choose to cross over to the exercise intervention arm after the eight week control period. Assessments will be completed at baseline and at eight weeks.

**Figure 1 F1:**
[figure not shown]
Flow diagram.

### Setting

The study will be based in Beaumont Hospital, Dublin. Assessments will be conducted in the Physiotherapy department and the exercise intervention will be completed in the participants’ homes.

### Participants

Patients will be recruited from medical and physiotherapy post Polio clinics and through advertisement in the national post polio support group publication. Eligibility criteria are shown in Table 
1. Information leaflets will be provided, as well as a detailed verbal explanation and questions answered. All potential participants will be screened for suitability by a medical doctor using the PAR-med-X screening tool. A letter will be sent to each recruited patients’ general practitioner, outlining the details of the study and requesting that they contact the researchers should they have any concerns about their patients’ participation. Prior to baseline assessment written informed consent will be obtained. Participants will be free to withdraw at any time.

**Table 1 T1:** Eligibility criteria

**Inclusion criteria**	
1	A history of Poliomyelitis affecting at least one lower limb, confirmed by the Neurologist
2	Capable of walking for 6 minutes, with or without an aid/appliance
3	Good upper limb strength, confirmed objectively using maximum voluntary isometric contraction, 7 out of 10 tested upper limb movements must lie above the 5th percentile of the normal range
4	Completion of the PAR-Med-X assessment and cleared by a medical practitioner as safe for exercise
5	Males/Females aged 18-75 years
**Exclusion Criteria**	
1	Unstable cardiac or respiratory conditions, including oxygen dependence
2	Uncontrolled hypertension
3	Significant upper limb pain. Greater than 4/10 on a Visual Analogue Scale or more than 3 specific sites of pain in the upper limbs, neck or upper back
4	Severe fatigue (greater than five on the Fatigue Severity Scale)
5	Recent onset of upper limb weakness or severe upper limb weakness
6	Steroid use in last 3 months
7	Pregnancy

### Sample size

The sample size for the study was determined based on a hypothesised change in heart rate of eight beats per minute, during the six minute arm test. Change in fatigue was also examined. The change in heart rate was based on reported changes in previous exercise interventions and considered clinically significant
[17,25]. For each calculation power was set at 80%, alpha at 5% and drop-out rate at 15%. The formula N= 2 [(standard deviation)^2^/(difference)^2^ x 7.9 was used. We aim to recruit 120 participants (60 per group). Table 
2 outlines the number of participants required based on the six minute arm test and the fatigue severity scale.

**Table 2 T2:** Sample size calculation

**Outcome measure**	**Clinically significant difference**	**Standard deviation**	**Number of participants required per group**
6MAT (Heart Rate)	8 b/m	14.5	60
FSS	1 point	1.1	48

